### Ethical approval and informed consent

Approval for the study was obtained from the hospital ethics committee, the Institutional Review Board, and the French Data Protection Authority (CNIL). Consent of the health care staff was sought prior to the study. The patients will be offered the opportunity to participate, and their consent (or, rather, non-refusal) will be written down in the medical file. As stipulated by French law, however, no signed patient consent will be required, given the study methodology and the type of intervention.

### Data analysis

Data analysis will be performed by the data management and analysis centre. The analyses will be carried out with the latest version of the R software environment. The lme4 package will be used to implement the generalised linear mixed-effects models. An intention-to-treat analysis will be performed at the cluster level, after the end of the last step (T7).

All of the characteristics collected will be subjected to a descriptive analysis. The comparability of the patients (between the intervention group and the control group, overall, at each time period and within each unit) will be verified.

The univariate analysis will consist in quantifying and testing the effect of the intervention on the proportion of patients undergoing an unscheduled rehospitalisation or an emergency visit.

First, the result criterion will be outlined within each unit and for each period (without the intervention, and then with the intervention). The average proportion will be compared between the two periods using a matched and weighted *t*-test in order to take into account the heterogeneous numbers of patients included in the various units.

As a second step, a mixed-effects logistic regression model with a random effect on the intercept will be used to model the probability of an unscheduled rehospitalisation or emergency visit taking into account the intra-cluster correlation. The effect of the intervention will be quantified using an odds ratio with a 95 % confidence interval. A random effect on the effect of the intervention can be added in order to quantify any heterogeneity of the impact among the units.

The possible evolution of the result criterion over time will be considered by integrating a period variable into the model, enabling the quantification of the effect of each time period with respect to a reference period (the first time period). In the event a tendency is highlighted, the period variable could be introduced into the model as an ordinal variable. This analysis will make it possible to quantify the effect of the intervention after adjusting for a possible time effect. Also, it will be possible to search for an interaction between time and the effect of the intervention.

The analysis can be adjusted on the patient characteristics that are likely to affect the result criterion.

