### Participants

The inclusion criteria are: patient hospitalised for 48 h or more in one of the short-stay geriatrics units participating in the study, aged 75 or older, living at home and with home as the planned place of discharge after admission, and at risk of hospital readmission or emergency visit after discharge. A patient will be considered to be at risk if he meets two or more of the following criteria (derived from the Triage Risk Screening Tool and from the 2013 French recommendations) [5, 13]:Problems in performing activities of daily living (assessed with the Index of Independence in Activities of Daily Living or ADL, and the Instrumental Activities of Daily Living or IADL), excluding the problem of urinary incontinence;One unscheduled hospital admission during the three previous months, or two or more unscheduled hospital admissions during the previous year;A geriatric syndrome such as: two or more falls during the 12 previous months, malnutrition (as defined by the French National Authority for Health), cognitive impairment (degenerative diseases, Alzheimer’s disease, or other dementia), or depression;One or more chronic diseases with high risk of acute decompensation or hospital readmission (i.e., chronic heart failure, chronic respiratory failure, etc.);Polypharmacy (defined as daily intake of five or more drugs); andAn unfavourable social situation (social exclusion, weakness regarding the home helper).

The exclusion criteria are:Patient living in a retirement home (i.e., a nursing home or a residential home for the elderly);Patient hospitalised at home;Patient living at home, but at a distance of 30 km (18 miles) or more from the hospital of index admission; andPatient already included previously in the study (each patient participates in the trial only once).

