### Sample size calculation

The number of patients has been determined according to a compromise between the inclusion ability of the units and the needed power, using the method of M.A. Hussey and J.P. Hughes [17]. The following hypotheses were used:A 30-day unscheduled hospital readmission or emergency visit rate after discharge of 20 % in the control group [2].A 10 % rate in the intervention group: the absolute risk reduction of the 30-day unscheduled hospital readmission or emergency visit rate ranges from 2.0 to 28.1 points according to previous studies with a bridging intervention based on a transition coach [18–24].A variation coefficient between clusters of 10 %. In cluster randomized trials, the variation coefficient is generally between 0.1 and 0.4. We have chosen a value of 0.1, because the variation of the outcome between units is supposed to be low. Furthermore, M.A. Hussey and J.P. Hughes have shown that, because the stepped wedge design uses both within-cluster and between-cluster information, power is relatively insensitive to variations of the coefficient of variation [17].

Under these hypotheses, for 6 clusters, 7 time periods, and an unilateral alpha risk of 5 %, the inclusion of 14 patients per cluster and per time period allows to reach a power of 70 %. The whole number of patients is 588. To allow for about 10 % missing data on the primary outcome, 15 patients per cluster and per time period will be included, for a total number of 630 patients.

A unilateral test has been chosen as it seems unlikely that exposure to the care transition program will increase the rate of unscheduled hospital readmissions or emergency visits within 30 days: these events are the result of hospital care factors, primary care factors, and patient factors. It does not seem possible for the intervention tested in this study to intensify the effect of these factors. The literature reviews do not report a significant increase in readmission rates associated with interventions on the hospital-to-home transition for older patients [5–8].

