## Discussion

### Discussion of the study design

A stepped-wedge trial presents methodological advantages [10, 11, 25, 26]. The clusters act as their own controls because they receive both the control and treatment conditions. Therefore, the intervention effect can be estimated from both between- and within-cluster comparisons. In addition, a stepped-wedge trial can take into account the changes in the main criterion over time (fluctuations in unscheduled hospital readmission or emergency visit rate) and enables the quantification of the effect of time on the effectiveness of the intervention (the learning effects).

This type of trial also presents benefits with regard to implementation [10, 11, 25, 26]. It allows the intervention to be administered successively in the participating centres, which can facilitate the organisation of a study in routine practice. The implementation of the intervention at regular time-step intervals also allows for improvement of the intervention or its delivery where necessary before the next implementation step, even if this may introduce differences in the intervention between clusters [10].

Indeed, learning effects may influence the effectiveness of the intervention [26]. First, the TN may become more experienced after enrolling each new cluster, which may lead to differences in the program (albeit small ones) between clusters. Subsequently, this may have an impact on the estimated intervention effect across clusters. Second, clusters will differ in the amount of time spent on the intervention. Eventually, clusters that switch at the first step will be more experienced with the intervention than clusters that switch at later steps. This may also influence the estimated intervention effect. Nonetheless, both types of learning effects can be modelled.

Finally, a stepped-wedge trial makes it possible for each participating centre to benefit from the intervention. This inclusiveness is a motivational factor for taking part in the study, and it also conforms to good ethical practice given that the intervention is expected to do more good than harm.

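### The tests that lead the primary analysis leave out calendar time, and the text does not say that the period-adjusted model governs

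*Protocol article*

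**What the plan says.** All references are to the protocol article.

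- **Time steps** and **Time frame**: all six clusters begin in the control condition, one crosses over at each 2-month step, and none goes back. There are seven periods over 14 months.
- **Data analysis**, first step: the section announces that the effect of the intervention on the primary outcome will be quantified and tested. It then describes the outcome in each unit for the phase without and the phase with the intervention, and says: "The average proportion will be compared between the two periods using a matched and weighted" *t*-test. The two periods here are the two phases, not calendar periods.
- **Data analysis**, second step: a logistic mixed model with a random intercept, giving an odds ratio and 95 % confidence interval. No time term is named at this point.
- **Data analysis**, later paragraph: "The possible evolution of the result criterion over time will be considered by integrating a period variable into the model". Each period is compared with the first, and period may become ordinal if a trend is seen.
- **Sample size calculation**: the Hussey and Hughes method with six clusters, seven periods and a one-sided 5 % level. The article says that "the inclusion of 14 patients per cluster and per time period allows to reach a power of"; the figure it gives is 70 %.
- **Discussion of the study design**: "a stepped-wedge trial can take into account the changes in the main criterion over time", offered as an advantage of the design.

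Nowhere does the article say which of these results decides whether the programme worked.

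**The concern.** In a stepped wedge, treatment and calendar time are tied together by design: early periods are mostly control, late periods mostly intervention. Randomising the order of rollout does not undo this. It makes clusters comparable within a period, and only an analysis that conditions on period uses that comparison. A paired comparison of each cluster's later phase with its earlier phase is a before/after study, and so, in large part, is a mixed model without period.

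If readmissions fall over the 14 months for reasons unrelated to the programme, these two analyses credit the fall to the transition nurse. If readmissions rise, they hide a real benefit. The unadjusted analyses also have the smaller standard error. A significant unadjusted result beside a non-significant adjusted one is therefore a realistic outcome, and the text gives no rule for that case.

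**Working it through.** **Inputs from the article.** Control rate 20 %, intervention rate 10 %, between-cluster coefficient of variation 0.1, 6 clusters, 7 periods, 14 analysed patients per cluster-period (6 × 7 × 14 = 588), one-sided 5 %. Any secular trend is an assumption, because the article gives none.

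**1. The plan's own power.** On cluster-period means, take V = (σ²/n)·I + τ²·J within a cluster, with σ² = 0.20 × 0.80 = 0.16, n = 14 and τ = 0.1 × 0.20 = 0.02. Power = Φ(0.10/SE − 1.645), with SE from generalised least squares.

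- With fixed period effects: SE = 0.0463; 0.10/0.0463 − 1.645 = 0.515; power 69.7 %. This is the stated 70 %.
- Without period effects: SE = 0.0338; 0.10/0.0338 − 1.645 = 1.314; power 90.6 %.

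Other variance choices do not rescue a version without period. At 14 per cell and one-sided 5 %, the lowest power found without period effects was 86.1 %, and that needed a coefficient of variation of 0.4. The trial was sized for the period-adjusted analysis.

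**2. Distance in time between the phases.** For a cluster that crosses over after period k of 7, the mean intervention period is (k + 8)/2 and the mean control period is (k + 1)/2. The difference is 7/2 = 3.5 periods for every k from 1 to 6, that is 7 months. A linear trend of b points per period therefore shifts the matched comparison by 3.5·b:

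- 0.25 point per period: 0.875 points
- 0.5 point per period: 1.75 points
- 1 point per period: 3.5 points, or 35 % of the planned 10-point effect

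**3. False-positive rate for benefit.** Simulated trials had 6 × 7 cells of 14 patients, a start at 20 %, coefficient of variation 0.1, no intervention effect and a one-sided 5 % level. The *t*-test was paired on the six clusters (5 degrees of freedom), with weights proportional to n₀n₁/(n₀ + n₁), where n₀ and n₁ are the patients in the two phases; the article does not give its weights.

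| Assumed decline per period | Matched *t*-test | Mixed model, no period | Mixed model, categorical period |
|---|---|---|---|
| 0 | 5 % | 4 to 5 % | 4 to 5 % |
| 0.25 point | 7 to 8 % | not run | not run |
| 0.5 point | 11 % | 11 % | 4 % |
| 1 point (20 % to 14 %) | 21 % | 21 to 23 % | 5 to 6 % |

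The mixed-model figures come from 1,000 to 1,800 simulated trials per scenario, so values near 5 % carry a Monte Carlo error of about half a point or slightly more. In the last row the model without period gives a median odds ratio of 0.81 although nothing happened; the model with period gives 0.98.

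**4. The opposite direction.** With a true fall from 20 % to 10 %, the *t*-test has power of about 82 to 83 % when there is no trend. An assumed rise of 1 point per period cuts it to about 46 %.

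**The case against.** The best defence is that the right analysis is already in the plan. The article states that a period variable will enter the model, with the first period as reference, which is categorical period in the random-intercept logistic model. It cites time adjustment as a reason for the design and sizes the trial on a time-adjusted variance. The section reads as a conventional progression from unadjusted to adjusted, and the second-step model may simply be the one that later receives the period term. Much of this stands. A reader might infer that the plan ignores calendar time, or that it sets up three rival confirmatory tests. The text supports neither, and the sample-size method is evidence of the right intention rather than another fault.

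Three parts of the concern survive. The *t*-test cannot be completed by a later period term, and it is described as part of testing the effect. The second-step model is presented with its own odds ratio and interval before time is mentioned. And the article fixes the order of the tests without saying which result governs. That is a stated rule that can mislead, not a detail left to a fuller document.

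Two other inferences should be resisted. One is that enrolling each patient only once builds in a downward trend by removing frequent readmitters. The article gives neither the size of the eligible pool nor its rate of renewal, so no trend can be derived. The other is that the *t*-test is further invalidated by pairing on nine units rather than six clusters. The pairing level is not stated outright, and the simulations here used six clusters, so they say nothing on it.

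**Conclusion.** The point holds in a limited form. The matched *t*-test and the model without period are not valid tests of effect in this design unless there is no secular trend, and the text leads with them. The offset of 3.5 periods is exact for every cluster. The inflation is conditional: none without a trend, about 11 % at a decline of half a point per period and about 21 % at 1 point, against a nominal 5 %. One point per period is a substantial assumption, 30 % relative over the trial (6/20), and should be read as the upper end of the range shown. A trend in the other direction costs power instead.

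The sample size and the period-adjusted model are consistent with each other and need no correction. What must be settled before the analysis is which result carries the conclusion.

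**What to change.** State in Data analysis that the single primary analysis of the primary outcome is the mixed-effects logistic model with intervention and categorical period as fixed effects and a random cluster intercept, fitted whatever trend is observed. Keep the display of proportions by unit and phase. Label the matched *t*-test and the model without period as descriptive and unadjusted, and do not present them as tests of effect. Because the primary form of period is then fixed in advance, any ordinal version becomes a secondary analysis.

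The cost is a change of wording. The standard error is larger than in the unadjusted analyses (0.0463 against 0.0338 on the risk-difference scale), but the stated 70 % power already allows for this. The 588 analysed and 630 included patients stay as they are. The Trial status section reports data collection under way, so the wording can be settled before any comparison is made.

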### Study design

This quasi-experimental study is a multicentre prospective, stepped-wedge cluster randomised trial with a continuous recruitment, short exposure design (participants are exposed for a short period with single measurement at a fixed time after the start of their exposure) [10–12].

The nine short-stay geriatric units will be grouped into six clusters (each cluster comprising one to two short stay units), taking into account their patient recruitment capacity and their geographic proximity. The six clusters will be divided into three geographic areas. The order of rollout will be randomised within each geographic area (see Fig. 1). There will be no randomisation between geographic areas.

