### Time steps

The study includes seven time steps (T0 to T6) with a 2-month period between steps. All clusters will start with the control situation (no care transition program) at the beginning of the study. At each time step, a new cluster will cross over from the control situation to the implementation situation. Each cluster will start the implementation of the program at a different time step. At T7, all clusters (and hence all hospitals) will have received the care transition program.

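### Six clusters are randomised and a cluster-level analysis is announced, but the matched t-test and the optional random intervention effect are written at the level of the nine units

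*Protocol article*

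**What the plan says.** All references are to the protocol article.

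- **Randomised entity (Study design).** "The nine short-stay geriatric units will be grouped into six clusters (each cluster comprising one to two short stay units"). On allocation: "The order of rollout will be randomised within each geographic area".
- **Crossover entity (Time steps).** "At each time step, a new cluster will cross over from the control situation to the implementation situation". Both units of a two-unit cluster therefore switch on the same date.
- **Powered entity (Sample size calculation).** Six clusters, seven periods, 14 patients per cluster and period, one-sided 5 %, 70 % power.
- **Declared level (Data analysis).** "An intention-to-treat analysis will be performed at the cluster level".
- **First-step summary and test (Data analysis).** "the result criterion will be outlined within each unit and for each period (without the intervention, and then with the intervention"). The two conditions are then compared with a matched t-test, weighted "in order to take into account the heterogeneous numbers of patients included in the various units".
- **Model (Data analysis).** "a mixed-effects logistic regression model with a random effect on the intercept" is to account for the intra-cluster correlation. The grouping factor of that intercept is not named. A random intervention effect may be added, and its stated purpose is to show how the impact differs among units.

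**The concern.** The randomised, switched and powered entity is the cluster, and the Data analysis section says so at its start. The first-step test and the optional random effect then move to the unit. In the three two-unit clusters, both units share a crossover date and were grouped partly by geographic proximity. The Discussion of the study design also expects the nurse's experience and the time spent on the programme to differ between clusters. A change common to both units would enter a unit-paired test twice, as if it were two independent observations. The test would then claim more information than was randomised, and its standard error and critical value would both be too small. An optional random intervention effect grouped by unit has the same weakness: two effects that may move together are treated as separate draws.

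**Working it through.** **1. The plan's own figure.** Closed-form stepped-wedge variance (Hussey and Hughes), with inputs from Sample size calculation: I = 6 clusters, T = 7 periods, 14 per cell, rates 20 % and 10 %, CV 0.1.

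- τ = 0.1 × 0.20 = 0.02, so τ² = 0.0004; s² = 0.20 × 0.80 / 14 = 0.01143.
- With one cluster switching per step: U = 21, W = 91, V = 91.
- Var = I·s²(s² + Tτ²) / [(IU − W)s² + (U² + ITU − TW − IV)τ²]
- = 6 × 0.01143 × (0.01143 + 0.0028) / (35 × 0.01143 + 140 × 0.0004) = 0.000976 / 0.456 = 0.00214
- SE = 0.0463; power = Φ(0.10/0.0463 − 1.645) = 69.7 %.

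The stated 70 % is reproduced on six clusters.

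**2. How many clusters have two units.** With a one-unit and b two-unit clusters, a + b = 6 and a + 2b = 9, so b = 3 and a = 3.

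**3. Degrees of freedom.** Nine unit pairs give 8, with a one-sided 5 % critical value of 1.860. Six cluster pairs give 5, with a critical value of 2.015.

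**4. Size of the first-step test.** Simulation with no true effect and 40,000 runs per row.

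- From the plan: 20 % rate, between-cluster CV 0.1, six clusters, seven periods, 14 patients per cluster and period.
- Assumed: paired units split the 14 equally; no time trend; a weighted t-test with weight 1/(1/n₀ + 1/n₁), where n₀ and n₁ are the numbers before and after crossover; and the SD of the cluster-specific before-after change.

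| SD of cluster-specific change | Nine unit pairs | Six cluster pairs |
|---|---|---|
| 0 | 5.1 % | 5.1 % |
| 2 points | 5.3 % | 5.2 % |
| 5 points | 6.0 % | 5.4 % |
| 8 points | 7.3 % | 5.8 % |

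The simulation error is about √(0.05 × 0.95 / 40,000) = 0.1 point, so the first two rows show no difference worth noting. If the shared disturbance is instead a cluster-by-period effect with SD 5 points, the figures are 5.8 % and 5.2 %. The largest gap in the scenarios run was 8.6 % against 6.4 %, at SD 8 with 14 patients in every unit. That case implies 9 × 7 × 14 = 882 patients, more than the 588 used for the power calculation.

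**5. Why the inflation is modest.** A unit that supplies 7 patients per period has a before-after difference with binomial SD √[0.16 × (1/21 + 1/28)] = 11.5 points at a 3:4 split of periods, and √[0.16 × (1/7 + 1/42)] = 16.3 points at 1:6. A shared change of 5 to 8 points is the smaller part of the variance.

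**6. Unit mix, as a hypothetical.** Suppose paired units lie one SD either side of 20 % at CV 0.1, so at 18 % and 22 %. Suppose also that 30 percentage points of the patients move to the lower-risk unit at crossover in all three two-unit clusters. Each such cluster changes by 0.30 × 4 = 1.2 points, and the average over six clusters is 1.2 × 3/6 = 0.6 points. A linear model with a cluster intercept gives 0.59 points. A random unit intercept gives 0.54. The planned effect is 10 points.

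**The case against.** The strongest reply is that the section already states a cluster-level analysis and a model for intra-cluster correlation, and that the power calculation uses six clusters. On this view the word unit is used loosely. The article never states nine pairs or 8 degrees of freedom. The t-test is a first, univariate step, and the odds ratio with its interval comes from the mixed model. Grouping factors are often left to the analysis plan, which is not shown.

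Much of this stands. A reader might infer that the whole analysis runs on nine independent units. The article does not support that: the level of the model's intercept is unnamed, and its stated purpose points to the cluster. Nine pairs is an inference from the wording of the summary and the weighting. The reply does not remove the point, because the article does more than omit a detail. It names one level and then writes the test and the optional random effect at another.

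A reader might also infer that a change in which unit supplies the patients will be read as a programme effect. The article does not support this as a bias that is present. It reports neither a change in unit shares at crossover nor a difference in risk between paired units. It also plans to check patient comparability by period and within unit, and it allows covariate adjustment. The two problems do not arise together either. In a unit-paired test each unit is its own control, so a mix shift cannot bias that unit's difference. With a cluster intercept, units that cross over together are not counted as separate clusters.

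**Conclusion.** The inconsistency of level is real and worth correcting, but its likely effect is small. If the pairs are the nine units, the one-sided 5 % error is about 6.0 % to 7.3 %, against 5.4 % to 5.8 % on cluster pairs, for an assumed SD of 5 to 8 points in the before-after change between clusters. That SD is not in the article, and it is 2.5 to 4 times the between-cluster SD of 2 points implied by the plan's CV. At an SD of 2 points or less the two levels are practically equal. The result also rests on the equal split within paired clusters and on the assumed form of the weighted test. No size is put on the optional random intervention effect; there the point is one of principle.

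The unit-mix shift remains a hypothetical risk of at most about 0.6 points at the plan's CV of 0.1 in the scenarios considered, and that figure also applies a between-cluster CV to units. The range of 0.1 to 0.4 in Sample size calculation describes cluster trials in general and is not the plan's own value, so larger biases computed from it should not be attributed to this plan.

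**What to change.** In the Data analysis section:

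- Base the matched, weighted t-test on the six randomised clusters, with 5 degrees of freedom. Unit-level proportions can stay as description.
- State that the random intercept is by cluster, and place any random intervention effect at cluster level too.
- Optionally add a unit term within cluster to absorb baseline differences between paired units, and say whether it is fixed or random. A random term rests on only three within-cluster contrasts and changes little at CV 0.1 (0.54 against 0.59 points in the hypothetical above).

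The cost is a change of wording and fewer degrees of freedom in the first-step test, with the critical value rising from 1.860 to 2.015. No new data are needed beyond each patient's unit and cluster. The Trial status section says data were still being collected, so the level can be fixed before the analysis.

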### Medico-economic study

The medico-economic study has a “piggy-back” design because it is added to the clinical study: the data necessary for the medico-economic study will be obtained from the detailed observation of the resources used for each patient included. Data collection will be done prospectively.

The medico-economic study will have two components.The first component will be a cost-effectiveness analysis of the main criterion assessed in the study. It will provide a cost per unscheduled hospitalisation or emergency visit prevented. The health insurance perspective is chosen. The time limit is 30 days after the index hospital discharge. The costs assessed will be direct medical expenses (hospital expenses, reimbursement of consultations or examinations, etc.), non-medical expenses (reimbursement of transport), and care transition program expenses (time spent by the TN for each patient at the three times of the transition).The second component will be a budgetary impact study of the implementation of the intervention. The time limit is 12 months after the index hospital discharge. Health insurance and societal perspectives will be considered. The costs assessed will be direct and indirect medical expenses (medical and social expenses, family expenses, institutional care expenses, etc.) and care transition program expenses. Various scenarios may be proposed in order to study the financial impact of the care transition program on the funders.

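### The period-adjusted effect is reported only as an odds ratio, so the one stated absolute comparison is a before-after contrast that absorbs any time trend

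*Protocol article*

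**What the plan says.** All four places are in the protocol article.

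- **Data analysis, first step.** The outcome is described by unit and phase ("without the intervention, and then with the intervention"), and then: "The average proportion will be compared between the two periods using a matched and weighted" t-test. The weights deal with unequal unit sizes. There is no term for calendar time.
- **Data analysis, second step.** A logistic model with a random intercept follows: "The effect of the intervention will be quantified using an odds ratio", given with a 95 % interval. A period variable is then added, of which the article says: "This analysis will make it possible to quantify the effect of the intervention after adjusting for a possible time effect". No other effect measure is named for the model.
- **Sample size calculation.** The target is a fall from a rate after "discharge of 20 % in the control group" to 10 % under the intervention. It is justified on the absolute scale: "the absolute risk reduction of the 30-day unscheduled hospital readmission or emergency visit rate ranges" from 2.0 to 28.1 points in earlier studies.
- **Medico-economic study.** The first component analyses the main criterion at 30 days: "It will provide a cost per unscheduled hospitalisation or emergency visit prevented".

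**The concern.** Two stated uses of the result are absolute: the 10-point target, and an economic ratio whose denominator is events prevented. An odds ratio alone supplies neither. The plan's only between-condition comparison on the absolute scale is the matched t-test, and in a staircase where every cluster goes from control to intervention that test cannot separate the programme from calendar time. The article itself counts the handling of fluctuations in the outcome rate among the strengths of the design (Discussion of the study design).

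At stake is the size of the reported absolute effect. If the before-after difference is read as that effect, or carried into the economic analysis, any trend is credited to the programme or charged against it, and the absolute result may disagree with the adjusted odds ratio.

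There is also a smaller point of labelling. The analysed criterion is the proportion of patients with an event, whereas the ratio is named per hospitalisation or visit. A patient with two visits counts once in the former and would count twice under the latter wording.

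**Working it through.** **Inputs.** 6 clusters, 7 two-month periods, 14 patients per cluster-period, 20 % against 10 %, coefficient of variation 0.1, one-sided 5 % (Sample size calculation). All clusters start in control and one crosses at each step (Time steps; Time frame).

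**1. The plan's own figure is on the absolute scale.** The Hussey-Hughes variance of a risk difference is

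Var = I·s²(s² + T·t²) / [(I·U − W)s² + (U² + I·T·U − T·W − I·V)t²]

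with I = 6, T = 7, U = 21, W = V = 91, s² = 0.20 × 0.80/14 = 0.01143 and t = 0.1 × 0.20 = 0.02. The numerator is 6 × 0.01143 × (0.01143 + 0.0028) = 0.000976. The denominator is 35 × 0.01143 + 140 × 0.0004 = 0.456. The SE is √0.00214 = 0.0463, and power = Φ(0.10/0.0463 − 1.645) = 69.7 %, against 70 % stated. The figure is reproduced.

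**2. What the odds ratio fixes.** The target corresponds to OR = (0.1/0.9)/(0.2/0.8) = 0.444. The same OR gives different absolute effects:

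| Control rate | Rate under OR 0.444 | Difference | Patients per event prevented |
|---|---|---|---|
| 14 % (Background; readmissions only) | 6.75 % | 7.25 points | 13.8 |
| 20 % (planned) | 10.0 % | 10.0 points | 10.0 |
| 25 % (assumed) | 12.9 % | 12.1 points | 8.3 |

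**3. Time gap in the matched contrast.** A cluster with i control periods (i = 1 to 6) has mean control period (i + 1)/2 and mean intervention period (i + 8)/2. The gap is 7/2 = 3.5 periods, or 7 months, whatever i is. Units of one cluster cross together, so no weighting of units removes it. This takes recruitment as even across periods, as planned.

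**4. Effect of a trend.** With a linear drift of d points per period, the contrast is −10 + 3.5d. The values of d are assumptions.

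| Assumed drift per period | Shift | Apparent reduction, upward drift | Apparent reduction, downward drift |
|---|---|---|---|
| 0.5 point | 1.75 | 8.25 | 11.75 |
| 1 point | 3.5 | 6.5 | 13.5 |

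**5. Does standardising the planned model remove it?** In a simulation (400 replicates per scenario, period-adjusted logistic model, assumed between-cluster SD 0.125 in log-odds, average over all seven periods), the drift was set in log-odds. A drift of 0.08 is about 0.08 × 0.2 × 0.8 = 1.3 points per period at a 20 % rate.

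| True effect, drift per period | Before-after | Standardised | Truth |
|---|---|---|---|
| none, −0.08 | −4.0 | +0.2 | 0 |
| OR 0.444, −0.08 | −11.3 | −8.7 | −8.4 |
| OR 0.444, +0.08 | −7.5 | −11.8 | −11.8 |

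The standardised difference follows the truth to within 0.3 point; the before-after contrast misses it by 2.9 to 4.3 points. The fitted model had no cluster term, so this checks the principle and not the exact planned fit.

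**The case against.** Several points on the other side are sound.

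- **The economic ratio is not shown to be biased.** A reader might infer that its denominator will be the t-test difference. The article does not say so. The Medico-economic study section gives perspective, horizon and cost categories but no effect estimator, and a condensed article may leave that to a fuller plan. Bias in the ratio is therefore conditional.
- **The model is not confined to an odds ratio.** It models a probability with a period term, so adjusted risks can be derived from it. What is limited is the stated reporting.
- **Comparison with the target is not impossible.** The trial will supply its own control rate, and the target can be expressed as OR 0.444. A reader might also infer that the test is compromised, but an odds ratio and a risk difference share the same null.
- **The t-test is only a first, univariate step.** The adjusted model follows it. That is so, but it remains the only stated between-condition comparison of proportions.
- **Tempting figures.** Pooling all cells gives mean periods of 56/21 = 2.67 and 112/21 = 5.33, a gap of 2.67 periods. That does not describe a test matched within units, where the gap is 3.5. One might also turn 6.5 and 13.5 points into a ratio 54 % too high (10/6.5) or 26 % too low (10/13.5). This holds the cost difference fixed, whereas hospital expenses are among the costs and would drift with readmissions, so these are not errors in the actual ratio.
- **The label.** The economic section does tie the analysis to the main criterion, so the mismatch is one of wording.

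**Conclusion.** The point holds as a mismatch between stated choices. The time-adjusted estimate is reported on the odds scale only, and the only absolute contrast named is confounded with time by construction. The 3.5-period gap follows from the design with even recruitment. The shift of 1.75 or 3.5 points on a 10-point effect rests on an assumed linear drift of 0.5 or 1 point per period, because the article gives no trend. A seasonal pattern would act differently from cluster to cluster. With no trend, the before-after contrast has no such bias.

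The documents do not support the claims that the cost-effectiveness ratio is biased as planned, that the odds-ratio test is invalid, or that the design or sample size must change. This is an inexpensive improvement to a stated analysis.

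**What to change.** 1. Keep the odds ratio. Add a risk difference from the period-adjusted mixed model: predict each condition's risk for every cluster and period, average over the trial's clusters and over periods 2 to 6, and subtract. Period 1 has no intervention patients and period 7 no controls, so including them would rest on extrapolation by the model.
2. Give the difference a 95 % interval by the delta method or by a parametric bootstrap from the fitted model. Resampling six clusters is unreliable.
3. State that the matched t-test is descriptive only.
4. In the cost-effectiveness ratio, use this risk difference together with a cost difference adjusted for period and cluster in the same way.
5. Label the ratio as cost per patient with an event avoided.

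The cost is a little analysis code and a few sentences; no new data or patients are needed. The adjusted difference will be less precise than the crude one. With the planning variance of 0.16 and 14 patients per cell, the time-adjusted SE is 4.63 points. The weighted before-after contrast has SE √(0.16/112) = 3.78 points, where 112 is the sum over clusters of 14ab/7, with a control and b intervention periods. The interval would be about 4.63/3.78 = 1.22 times as wide.
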